# Pulmonary Function and Sleep-Related Disorders During Cervical Administration of Intrathecal Baclofen in Adults With Spinal Cord Injury (Cervit-B): Protocol for a Multiphase Single-Arm Intervention Trial

**DOI:** 10.2196/70362

**Published:** 2025-08-14

**Keywords:** spinal cord injury, spasticity, intrathecal baclofen, upper extremity, pulmonary function, sleep-related disorders

## Abstract

**Background:**

The effect and safety of intrathecal baclofen (ITB) on generalized spasticity of the lower extremity have been well described in numerous studies, whereas the safety and effect on spasticity of the upper extremity during cervical administration seems to be less certain.

**Objective:**

We aim to establish the safety of cervical administration of ITB on pulmonary function and sleep-related disorders in adults with a cervical spinal cord injury with functional hindering spasticity. In addition, we aim to explore the effect of cervical ITB on the reduction of spasticity; participant satisfaction; and improvement at the level of function, activities, and participation.

**Methods:**

The study is a multiphase single-arm intervention study. Before the start of the study, participants are screened for the presence of sleep-related disorders, and pulmonary function is assessed using spirometry and a capillary blood gas sample. Participants are allowed to start the first phase of the study if there are no signs of sleep-related disorders or if these are adequately treated. The P_c_CO_2_ (partial pressure of CO_2_ in capillary blood sample) should be between 4.5 and 6.5 kPa. In the first phase of the study, an extracorporeal pump will be used to investigate whether cervical administration of ITB leads to a reduction of spasticity without an adverse effect on pulmonary function and sleep-related disorders. In case of a safe (no adverse effects) and positive (reduction of spasticity) result of the trial, a baclofen pump will be implanted in the second phase of the study. After implantation, the dosage of ITB will be slowly increased, and eventually, the use of oral spasmolytics will be phased out. The dosage will be increased during the monitoring of pulmonary function and sleep-related disorders. In the second phase of the study, a pulse oximetry will be performed, and pulmonary function; spasticity; satisfaction; and the level of function, activities, and participation will be assessed at 3, 6, and 12 months after definitive implantation of the baclofen pump.

**Results:**

The first participant was recruited on May 23, 2023. Data collection and analyses are expected to be completed in 2027.

**Conclusions:**

Currently, little is known about the safety and effectiveness of cervical administration of ITB for the treatment of upper extremity spasticity. We aim to establish the safety and explore the efficacy of this procedure. This paper describes the protocol of this study.

**International Registered Report Identifier (IRRID):**

DERR1-10.2196/70362

## Introduction

### Background

Cervical spinal cord injury (SCI) is often accompanied by spasticity of the upper extremity (UE), leading to limited function of the UE, which may negatively influence the quality of life [1]. Therefore, effective treatment of spasticity is of great importance. Neuromuscular blocks or surgery are treatments for focal spasticity. Neuromuscular blocks might be insufficient for generalized spasticity, given the maximum tolerated dose and potential complications [2]. Baclofen therapy is well established for the treatment of generalized spasticity [2]. Baclofen is a strong and selective gamma-aminobutyric acid-B receptor agonist, leading to presynaptic inhibition of reflex activity. Dosing the baclofen directly into the spinal fluid results in a higher drug concentration at the site of action, with fewer systemic side effects compared to oral baclofen. The effect of intrathecal baclofen (ITB) on generalized spasticity of the lower extremity (LE) has been well described in numerous studies, whereas the effect on spasticity of the UE seems to be less certain [2,3]. This difference in effectiveness might be related to the placement of the catheter tip intrathecally and the baclofen gradient in the cerebrospinal fluid [4,5]. In current settings, the catheter tip is usually placed at the thoracolumbar level.

It has been shown that the concentration of baclofen is highest around the tip of the catheter and the concentration rapidly decreases in caudal and rostral direction [4,5]. Furthermore, the rate of decrease depends on the method of infusion (bolus or continuous). There is a faster decrease in concentration in continuous infusion [5].

As the catheter position affects the concentration gradient, the concentration of ITB at the cervical level will be higher if the catheter tip is at the cervical level than if the catheter tip is at the thoracolumbar level. To properly treat spasticity of the UE, the tip of the catheter should be positioned cervically. A cervical catheter tip will probably, in addition to the effect on spasticity of the UE, also have an effect on the spasticity of the respiratory muscles.

Reducing the spasticity of respiratory muscles could improve respiration and pulmonary function [6-8]. However, higher concentrations of ITB at the cervical level may lead to a deterioration of pulmonary function and an increased risk or increased severity of sleep apnea syndrome (SAS) due to respiratory muscle weakness and a central dampening effect [3].

A systematic review by Jacobs et al [9] suggests that cervically administered ITB seems to improve UE spasticity and function, without causing more complications than thoracolumbar ITB. However, the main drug-related complications have not been thoroughly investigated, preventing definitive conclusions [9]. This conclusion is confirmed in a recent study by Mossner et al [10]. Therefore, we propose investigating the safety and exploring the efficacy of this procedure.

### Objective

We aimed to extensively describe the design and methodology of the Cervit-B study, in which we will investigate the safety of cervical administration of ITB in adults with SCI. In addition, we will explore the effect of cervical ITB on spasticity; the level of function, activities, and participation; and participant satisfaction. We hypothesize that cervical administration of ITB is a safe procedure without adverse effects on pulmonary function, as measured by spirometry and capillary blood gas, and on sleep-related disorders in the sense of SAS. In addition, we hypothesize that it improves the efficacy of spasticity management, enhances functional abilities and activities, promotes greater social participation, and increases participant satisfaction.

## Methods

### Study Design

This multiphase single-arm intervention study will contain 2 phases. We will first start with screening and recruitment to determine if there is an indication for, and if it is safe to start treatment with ITB. Phase 1 will be the safety phase, in which an extracorporeal pump will be used to investigate whether cervically administered ITB leads to reduction of spasticity without adverse effect on pulmonary function and sleep-related disorders. In case of a safe and positive test, we will continue to the next phase (phase 2) in which a baclofen pump is implanted. After implantation, the dosage of ITB will be slowly increased to the optimal setting, and if the participant uses oral spasmolytics, these are phased out. The optimal setting varies in accordance with patient conditions. In this phase of the study, we will focus, in addition to pulmonary function and sleep-related disorders, on the reduction of spasticity; improvement of participants’ level of function, activities, and participation; and participant satisfaction according to the International Classification of Functioning [11].

All participants will be assessed once before the start of phase 1 (T0A1), at the start of phase 1 (T0A2), and daily during phase 1 (T0B). In the case of a safe and positive test, participants will be assessed at the end of phase 1 (T1). During phase 2, they will be assessed at 3, 6, and 12 months (T2, T3, and T4) after baclofen pump implantation. We chose to start the assessment in phase 2 only after 3 months following the implantation because in the first 3 months, the pump settings will still be regularly adjusted to optimize the daily dosage of ITB.

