Daily capillary blood gas samples will be taken, and continuous pulse oximetry during sleep, by use of the OSAsense, will be recorded. If the participant is set on a continuous positive airway pressure (CPAP) device, the CPAP device is read out. The trial will be determined as unsafe and will be stopped if the P_c_CO_2_ is >6.5 kPa for 2 days in a row, according to hypoventilation rules in adults as mentioned by Berry et al [28]. The trial will also be stopped when participants without SAS, during the trial, will develop complaints matching SAS and the Oxygen Desaturation Index (ODI) is between 5 and 15 [27]. The ODI represents the number of desaturations per hour.

A third reason to stop the trial is when participants during the trial have no complaints matching SAS, but the ODI is >15 [27]. If the participant uses a CPAP device, the setting of the device may be adjusted to stay within the safety margin. This safety margin is set at an AHI <5 [24]. This adjustment will be registered. A fourth reason to stop the study is when, after adjustments of the CPAP device, it is not possible to stay within this safety margin [24]. A fifth reason to stop the study is if there is no effect on spasticity at the maximum dose of ITB (200 µg per day).

If the participant experiences a positive effect of the ITB on their spasticity, with a score between 1 and 3 on the Patient Global Impression of Change (PGIC) [29] without deterioration on functionality (PGIC 5-7) and there is not a clinically relevant deterioration of pulmonary function or SAS, it is considered a safe and positive ITB trial with an indication for intracorporeal pump implantation (phase 2) and treatment with ITB at cervical level. We opted for these cut-off values for assessment of reduction of spasticity according to the algorithm established by the European working group for spasticity in adults [30].

If, during the trial, no effect is observed on spasticity or there is a clinically relevant deterioration of pulmonary function or SAS, the trial will be discontinued. This is considered a negative test in which there is no indication for treatment of spasticity with ITB. The catheter and the subcutaneous infusion port will then be removed (Figure 2)*.*

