**Participants and disease characteristics**																				
	Sex	✓																		
	Race	✓																		
	Age	✓																		
	Level and completeness of the SCI^r^	✓															International Standards for Neurological Classification of Spinal Cord Injury			
	Etiology of SCI	✓																		
	Time since injury	✓																		
	Other treatments against spasticity	✓																		
	Medication	✓		✓		✓		✓		✓			✓		✓					
	Comorbidity	✓		✓		✓		✓		✓			✓		✓					
	Vital signs	✓		✓		✓		✓												
	Complications and side effects			✓		✓		✓		✓			✓		✓					

^a^T0A1: preassessment screening.

^b^T0A2: start of the extracorporeal pump.

^c^T0B: period during the trial phase.

^d^T1: moment appropriate titration in the trial phase.

^e^T2: 3 months after implantation.

^f^T3: 6 months after implantation.

^g^T4: 1 year after implantation.

^h^If there is any suspicion of sleep apnea syndrome based on the results of the pulse oximetry, additional polysomnography will be performed during the screening and recruitment.

^i^If participants during the trial phase experience dyspnea, spirometry will be performed.

^j^PGIC: Patient Global Impression of Change.

^k^PRPM: Perceived Resistance to Passive Movement.

^l^MAS: Modified Ashworth Scale.

^m^MRC: Medical Research Council.

^n^ROM: range of motion.

^o^COPM: The Canadian Occupational Performance Measure.

^p^GRT: Grasp and Release Test.

^q^QIF-sf: Quadriplegia Index of Function—Short Form.

^r^SCI: spinal cord injury.

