### Statistical Analysis

Because of the small sample size, it is expected that the continuous variables will not be parametrically distributed; therefore, they will be presented as median with IQR. Furthermore, due to the small sample size, pre- and postassessments during the first phase or the ITB trial phase will be compared with descriptive statistics and differences will not be formally tested. In addition, the measurements in the second phase after definitive implantation of the baclofen pump (3, 6, and 12 months after implantation) will be compared with descriptive statistics. Changes over time in the outcome measures within patients will be visually explored.

For categorical variables, we will present numbers and corresponding percentages. To compare pre- and postassessment during the first phase or the ITB trial, cross tabs will be made. Our primary analysis population is the intention-to-treat analysis. Considering the study design, we expect a few missing data. In case of missing data, we will use generalized estimation equations analysis (<20% missing data) or multiple imputations (>20% missing data).

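### Spirometry during the phase 1 infusion is scheduled only for participants whose test was safe and positive, so the phase 1 spirometry comparison omits those who were stopped and can lean towards safety

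*Protocol article*

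**What the plan says.** Study Design gives the early assessments, including the daily T0B ones, to everyone without condition: "All participants will be assessed once before the start of phase 1 (T0A1), at the start of phase 1 (T0A2), and daily during phase 1". The next sentence narrows the group: "In the case of a safe and positive test, participants will be assessed at the end of phase 1 (T1"). Table 1, footnote d, agrees, defining T1 as the "moment appropriate titration in the trial phase", a point that a stopped trial need not reach.

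The phase 1 schedule in Table 1 differs by measure:
- **Capillary blood gas:** T0A1, T0A2, T0B and T1.
- **Pulse oximetry:** T0A1 and T0B, not T1.
- **Spirometry:** T0A1, T0A2 and T1, not T0B. Footnote i adds: "If participants during the trial phase experience dyspnea, spirometry will be performed".

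All three stand under primary outcomes in Table 1. The Objective section names spirometry together with capillary blood gas in the safety hypothesis.

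The section ITB Trial (Phase 1) provides the daily safety data: "Daily capillary blood gas samples will be taken, and continuous pulse oximetry during sleep, by use of the OSAsense, will be recorded". It lists stopping reasons based on PcCO2, ODI, AHI under CPAP and lack of effect on spasticity. A trial counts as safe and positive only if, among other things, "there is not a clinically relevant deterioration of pulmonary function or SAS".

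Statistical Analysis states that "pre- and postassessments during the first phase or the ITB trial phase will be compared with descriptive statistics", without formal testing and without naming the post time point. It adopts intention-to-treat, expects few missing data, and names generalized estimating equations below 20% missing and multiple imputation above 20%.

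**The concern.** Whether the phase 1 post-infusion spirometry is taken depends on the result of phase 1. A participant stopped for raised PcCO2 or for sleep-disordered breathing has pre-infusion spirometry but no scheduled spirometry on infusion. If that person's vital capacity fell without dyspnea, the fall is never recorded. The Introduction names respiratory muscle weakness as a feared mechanism, and spirometry is the scheduled test that addresses it most directly.

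There is also an ordering problem. Deterioration of pulmonary function is one ground for calling a trial unsafe, yet routine spirometry is due only after the trial has been called safe and positive. It cannot inform that decision unless dyspnea has prompted an extra test.

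At stake is a favourable-looking spirometry summary from the safety phase of an 11-person study. Values not taken during infusion cannot be recovered later.

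**Working it through.** The plan states no figure for this point. Sample Size says that no calculation was done and takes 11 participants from an earlier comparable study, so there is nothing to reproduce. The check has two parts.

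**1. Who has an on-infusion value in phase 1, by measure**

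| Measure | Success | Stopped (unsafe or no effect) |
|---|---|---|
| PcCO2 | T0B daily, T1 | T0B daily until stopping |
| ODI, or AHI from CPAP | T0B nightly | T0B nightly until stopping |
| Spirometry | T1 | none, unless dyspnea |

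The gap is confined to spirometry. For PcCO2 it opens only if the analysis takes T1 alone as post. For the sleep markers it cannot arise, because oximetry is not scheduled at T1.

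**2. Illustration of size**

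Document input: n = 11 starting phase 1. Assumed inputs: the proportion p stopped (10% to 50%), and the correlation rho between spirometry change and the tendency to be stopped (0, 0.5, 0.8).

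*How many lack T1.* The expected number with T1 is 11(1 − p). The chance that at least one lacks it is 1 − (1 − p)^11; for example, 1 − 0.9^11 = 0.69. Since 2/11 = 18% and 3/11 = 27%, three or more missing crosses the plan's 20% threshold.

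| p | Expected with T1 | P(at least 1 without) | P(3 or more without) |
|---|---|---|---|
| 10% | 9.9 | 69% | 9% |
| 20% | 8.8 | 91% | 38% |
| 30% | 7.7 | 98% | 69% |
| 50% | 5.5 | >99% | 97% |

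*How far the T1-only mean is shifted.* If the worst fraction p on a normal stopping tendency is removed, the mean change in those remaining is too favourable by rho × φ(z_p)/(1 − p), in SDs of the change. At p = 30%: φ(−0.524) = 0.348; 0.348/0.70 = 0.497; × 0.5 = 0.25 SD.

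| p | rho 0 | rho 0.5 | rho 0.8 |
|---|---|---|---|
| 10% | 0 | 0.10 | 0.16 |
| 20% | 0 | 0.175 | 0.28 |
| 30% | 0 | 0.25 | 0.40 |
| 50% | 0 | 0.40 | 0.64 |

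Simulation gives the same values to within 0.01. With a true mean change of −0.5 SD, p = 30% and rho = 0.5, those with T1 would show −0.5 + 0.25 = −0.25 SD. With spirometry in everyone at the end of infusion, this shift is zero.

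**Blood gas, only if T1 alone were post.** Assume baseline PcCO2 about N(5.5, 0.45) kPa within 4.5 to 6.5, and a true rise of 0.50 (SD 0.50). Stopping on one reading above 6.5 removes 22% and leaves a mean rise of 0.35. The protocol's rule needs two days in a row. With 50% to 70% of the variance in the rise assumed to lie between persons, 13% to 15% are stopped and the mean rise is 0.43 to 0.41. If the last T0B value is used for everyone, this selection disappears.

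**The case against.** The strongest reply is that the plan's named safety markers do not depend on T1. Primary Outcome Measures bases safety on blood gas and OSAsense or CPAP data from before and during phase 1, with PcCO2 and AHI or ODI as markers. Everyone has these daily, and participants are stopped because of them. **This stands.** A reader might infer that the whole phase 1 comparison leaves out those who deteriorated, or that the design cannot show harm. The documents do not support that: meeting a stopping criterion is itself an observed harm, side effects are recorded at T0B, and the data safety monitoring board assesses safety after six participants.

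Second, the post time point may be named in a full protocol or analysis plan that is not shown. This stands for blood gas, which is why that part is conditional. It does not help spirometry, because no choice of time point supplies a measurement that was not scheduled.

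Third, spirometry is not among the named safety markers, and its procedure is described under Secondary Outcome Measures. That lowers the weight of the point. Table 1 nevertheless lists it as primary, and the hypothesis names it.

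Fourth, safe can be decided on PcCO2, ODI and AHI without spirometry. This stands, so the ordering problem is limited to spirometry and does not make the whole safety decision circular.

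Fifth, Results reports 6 participants in phase 1 and 3 in phase 2. A reader might infer that half lack T1. The counts do not show this: the others may be in progress, awaiting implantation, or stopped for lack of effect.

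**Conclusion.** The point holds for spirometry. Followed exactly, the plan leaves every stopped participant without dyspnea without on-infusion spirometry, and the descriptive phase 1 comparison then rests mainly on successes. The direction is towards safety if stopping is related to worse lung function. The size is unknown: those stopped for lack of effect also lose T1, and dyspnea-triggered tests recover some values selectively. The range of 0 to 0.64 SD rests wholly on assumed stop rates and correlations.

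The intention-to-treat label does not supply values that were never measured. Absence caused by the outcome is also not the sporadic missingness that the plan expects, and imputing from successful participants would carry the selection forward.

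For blood gas the same selection arises only if T1 alone is used as post. The ODI and AHI comparison is not affected. This is a gap in one Table 1 primary outcome. It does not undermine the PcCO2 and AHI/ODI safety assessment, but it merits a prompt amendment because the missing values cannot be obtained later.

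**What to change.** 1. Amend Study Design and Table 1 (including footnote d) so that spirometry is taken at the end of infusion in every participant who starts phase 1, whatever the reason for ending and where clinically possible.
2. In Statistical Analysis, define the phase 1 post value for blood gas and AHI/ODI as the last on-infusion value (T0B or T1) in all who started. The worst value should be at most a supplementary description. Set against a single baseline reading, it creates apparent deterioration without any effect: the expected maximum of 3, 5 or 7 independent readings lies 0.85, 1.16 or 1.35 within-person SDs above the person's mean.
3. Report the number meeting each stopping criterion out of all who started phase 1, and state how many have no on-infusion spirometry and why.

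The cost is a short amendment and one extra handheld spirometry in the few inpatients who are stopped, using a test already in the schedule. Items 2 and 3 need no new data. No dose or stopping rule changes. Participants already stopped without the test cannot be recovered and should be reported as such.

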### Setting

The study settings of phases 1 and 2 will be at the Medisch Spectrum Twente (MST) hospital and Roessingh Center for Rehabilitation (RCR), respectively. Both the centers are in Enschede, the Netherlands.

### Study Coordination

RCR is the coordinator of the study and is responsible for the study design, management, data collection, and data analysis.

A data safety monitoring board is involved throughout the study. Once the first 6 participants have completed phase 1, the board will assess the safety and related continuation of the study. Monitored visits by an independent study monitor are planned every 6 months. This is to ensure the continued protection of participants’ rights and well-being, assure protocol adherence, and verify that data integrity during the study complies with good clinical practice [12]. All protocol deviations will be filed. In this study protocol, the SPIRIT (Standard Protocol Items: Recommendations for Interventional Trials) reporting guidelines are used [13].

### Ethical Considerations

The study will be conducted according to the principles of the Declaration of Helsinki, (October 2013 version), and in accordance with the Medical Research Involving Human Subjects Act (WMO). Approval of the study has been obtained from the Medical Ethics Committee Oost Nederland (2021-7364) and the Central Committee on Research Involving Human Subjects. The trial is registered in the EudraCT database (2021-004994-30) and is transitioned to the Clinical Trials Information System (2023-508143-51-01). All administrative and protocol-related amendments will be submitted for approval to the Medical Ethical Committee. After receiving their approval, these modifications will be reported via email to the participating centers and the external monitor. The sponsor has both patient and liability insurance, which is in accordance with article 7 of the WMO.

After the nature and possible consequences of the study are explained, informed consent will be obtained from all participants. Participants will be informed that they always have the ability to opt out. Apart from travel expenses, there is no compensation for the participants.

Before the start of the study, a data management plan that covers all aspects of handling data gathered during and after completion of the study was devised.

All documents related to the study and all participants’ data will be collected in the investigators’ site files. These files, containing personal and contact information, as well as the screening information from potential candidates, will be safeguarded in RCR. All relevant data will be copied from the case report form into a web-based clinical database for case report data (Castor, Castor EDC) by the primary investigator using unique and anonymous participant codes. If necessary, this study identification number can be linked to the participant by the primary investigator only. The primary investigator, the research assistant in RCR, the research nurse in MST, and the monitor will have access to the full dataset.

All coded data will be stored for 10 years within the clinical database.

